## **Protocol**

### **Title: Pregnancy and water exercise**

#### **Introduction**

During pregnancy up to 50-75% of all pregnant women experience low back pain in the Scandinavian countries (1-4). It is problematic on both personal and socio-economic level, as low back pain reduces the possibilities to carry out daily activities (5, 6). Moreover, low back pain is associated with both increased risk of sick leave during pregnancy and low back pain after birth (7-11). A report from the Danish Ministry of Employment showed that almost 2/3 of all pregnant women were on sick leave beyond the last four weeks before the birth, where all pregnant women have the right to maternity leave (12).

Few and very different studies worldwide have investigated whether low back pain during pregnancy can be prevented or reduced (13-18). Many women reduce physical activity level during pregnancy and discontinue strenuous physical activities (19-21), as they find it unsafe or uncomfortable to perform during pregnancy (22; 23). Many women find it pleasant to perform activities such as swimming or water gymnastics and studies have shown that these activities increases temporarily during pregnancy (19; 23). On this basis, we want to investigate whether exercise activities in water have a positive effect on low back pain and sick leave during pregnancy.

Our hypothesis is that a part of the pain can be prevented or reduced by moderate exercise during pregnancy. The Danish Rheumatism Association has developed the AquaMama concept for pregnant women. AquaMama concept consists of six exercises designed specifically for pregnant and intended for unsupervised exercise in water. The tools necessary for performing the exercises are available in more than 130 public swimming pools in Denmark. Furthermore, many lifeguards are certified AquaCoaches and can supervise and advise the pregnant women while performing the exercises.

In this study we will therefore investigate whether water exercise with the AquaMama concept during pregnancy has an effect on the intensity of low back pain and the number of days of sick leave.

We expect that this study leads to new knowledge about whether the exercise in water can affect the pregnant woman's low back pain and sick leave in a positive way. The new knowledge can be used in antenatal care in Denmark. Furthermore, it is our hope that the new knowledge can be an inspiration in municipalities and workplaces.

#### **Background**

Low back pain is experienced in up to 50-75% of all pregnant women in the Scandinavian countries (1-4). The pain is costly, as it affect the pregnant woman's ability to perform daily activities (5; 6) and is associated with sick leave. Previous studies have shown that a high proportion of days spend on sick leave is related to pain in the musculoskeletal system, and that more than 25% of the days spend on sick leave during pregnancy can be attributed to low back pain (10; 11). Several studies have shown that low back pain during pregnancy is associated with low back pain for several years after birth (7; 8; 24). Few studies worldwide have investigated whether low back pain in pregnancy can be prevented or reduced (13-18).

The National board of Health recommends that healthy pregnant women should be moderately

physically active at least 30 minutes a day (25). Physical activity during pregnancy reduces the risk of many pregnancy and birth complications (25-29). However, the majority of women decrease their physical activity level during pregnancy compared to before pregnancy, and many stop strenuous exercise activities (19-21). Causes may be the growing body complications or insecurity. Activities such as swimming and water exercise is the type of activities which increases during pregnancy, and pregnant women feel comfortable performing it.(19; 23; 30; 31). Recent studies have shown that swimming during pregnancy was not associated with higher risks for pregnancy complications (32; 33). The National Board of Health recommends non-weight-bearing physical activity for women with back or pelvic pain (25).

While the explanation for low back pain during pregnancy can be attributed to some muscle groups are more relax while others become more tense as a result of a change partly to the body's center of gravity and a woman's weight (34), it is obvious that physical activities, especially physical activities in water, which gives the pregnant woman a greater ability to move (23) may reduce the intensity of low back pain. It is important to distinguish between low back pain, and pelvic girdle syndrome, as the prognosis and the treatment is different (39). Pelvic girdle syndrome occurs in approximately 5% of pregnant women in Denmark, usually occurs around week 20 and gradually worsened during pregnancy (40). Pelvic girdle syndrome is defined as pain localized to the 3 sacroiliac joint. The prognosis for pelvic girdle syndrome is worse than for low back pain, as about 20% is still not free of pain two years after birth (41). Pelvic girdle syndrome is diagnosed by a physiotherapist, performing an examination of joints and muscles of the pelvic region, to ensure that the pain is joint- related and not muscular.

The evidence on the prevention and reduction of low back pain during pregnancy is very limited. Two Swedish studies found positive effects of exercise in water during pregnancy on low back pain, pelvic pain and sick leave (14; 35). A weakness in one study was that there were included women with both low back pain and pelvic pain (14). As the two syndromes have different etiology, treatment and prognosis, it may be misleading to assess the effect as a whole. Neither of the two studies described the intervention in details, which is necessary if the studies, is to be reproduced. In both studies the training took place at specific time, during daytime, and participants indicated having difficulty to follow a specific team. In one study the water training (intervention) took place in hot water (35), such a study is not possible to appliqué in Denmark as hot pools only exist in a limited number in Denmark.

We believe that the Aqua Mama program is a suitable for an intervention study in Denmark. Unlike the Swedish studies, it is a form of intervention that is individual and can be adapted to work and family and Aqua Mama can take place in a normal public swimming pool. It is important to test a program that is available (geographic / economic) for all pregnant women. The standardized Aqua Mama exercise series is developed by professionals, so the woman has a sense of security by conducting the exercises. A standardized training program also increases the generalizability.

### **Hypothesis and objectives**

The hypothesis is that water exercise with the Aqua Mama program twice a week of 45 minutes duration for 12 weeks during pregnancy will reduce the intensity of the pregnant woman's lower back pain and reduce the number of days of sick leave.

The project objective is to investigate the effect of water exercise with Aqua Mama program during pregnancy on the intensity of low back pain and duration of sick leave.

## Method

### Design

The study is built up as a randomised controlled study of pregnant women with unsupervised exercise with the Aqua Mama program as intervention. The women are randomized in a ratio of 1:1 for the two groups (intervention versus control). Randomisation is via a specially designed computer system. Randomization is pre-arranged with the Centre for Public Health and Quality (CFK), Central Jutland, where randomization will be stored.

### Participants'

Healthy pregnant women with a normal pregnancy with a single fetus.

Inclusion Records Does the:

- 1) Women  $\geq 18$  years
- 2) Informed consent
- 3) Gestational age 14-17 weeks
- 4) and understand Danish
- 5) Women with BMI  $\leq 29$  kg/m^2
- 6) Pregnant women with a chronic disease before pregnancy is offered first participation by prior arrangement with the obstetrician at the hospital
- 7) Can swim 50 meters

Exclusion criteria:

- 1)  $< 18$  years
- 2) Multiple pregnancies
- 3) Abuse Problems
- 4) Pelvic girdle syndrome in previous pregnancies (diagnosed by physical therapist or doctor)
- 5) Conditions or chronic diseases where physical activity is contraindicated

### Intervention

Participants are offered:

- an introduction session with a midwife, physiotherapist and Aqua Coach on water exercise with the Aqua Mama program
- There will be introductory sessions each month. There will be a midwife or physiotherapist present at all sessions
- Women are encouraged to exercise with Aqua Mama program twice per week by 45 minutes duration of 12 weeks.

**Content and dosage of self-training:** The pregnant participants perform six exercises like circuit training in two series. In each series performed Mama Surf 2 x 20-30 times, Mama Pendulum 2 x 15-20 times, Mama Boxing 2x15-20 times MamaBiceps 2x15-20 times, Mama Lift 2x10-12 times and Mama Jogging 2x2 min and exercises done at a steady pace Furthermore the participants will swim 4 laps before and after the exercise program (200 m total). The program has been tested by a physiotherapist.

The exercises can be found at:

<http://www.gigtforeningen.dk/aquapunkt/aquamama+%c3%b8velser>.

- Each month there will be a brush-up session for participants, at the session there will be a Aquacoach, a midwife and physiotherapist present in the swimming pool.
- Providing a free voucher with 12 tickets to the swimming pool.

In order to support the compliance and adherence, the following is carried out (23, 44-45):

- 1) The participants assembled and introduced to each other at the introduction session
- 2) Participants receive weekly motivational SMS and e-mails from project midwife
- 3) Participants can see graphs with each other's training sessions on the website. This is optional and for those women who want a little competition.
- 4) There will be created a Facebook group where participants can give each other ideas and share experiences with the exercises and find training partners
- 5) Via e-mail or SMS participants send messages to project the midwife about the number of training times per week as well as experiences with training

### **Indications for treatment stops**

- PPROM (Rupture of membranes before the 37th week of pregnancy)
- Symptomatic placenta praevia
- Pelvic girdle syndrome, diagnosed by a physiotherapist from international guidelines
- Vaginal Bleeding
- Threatening premature birth
- Preeclampsia

### **Control group**

Will receive general guidance and advice on exercise as part of standard prenatal care. The control group will receive two free tickets for baby swimming, when the final questionnaire has been filled out at follow up.

### **Outcome variables / endpoints**

Outcome variables / endpoints measured in the 32nd week of pregnancy. Primary end-point is the intensity of low back pain.

Secondary end-points are: Sick leave (yes / no), number of days and the cause of sick leave, physical disability and general health experienced in the 32nd week of pregnancy.

### **Questionnaire (Measured at baseline and at 32 weeks of gestation)**

The participants will be presented with a drawing of a women where the definition of low back pain is illustrated.

### **Low back pain rating Scale**

Is designed to detect changes in the level of pain in the low back (36). It consist of a 11-point box scales. 3 scales measuring pain "just now", "the worst back pain" within the last 14 days and "average" back pain within the last 14 days. Highest figures represent the worst pain (36).

### **Sick leave**

The number of days of sick leave and cause / causes of absenteeism are stated

### **Roland Morris Disability Questionnaire (RMDQ)**

Roland Morris Disability Questionnaire (RMDQ) is a questionnaire investigating functional capacity in patients with low back pain. The scale measures the impaired function due to back problems. It consists of 23 questions that are answered with yes / no. Is given the maximum 23 points, where the highest score indicates worst disability (37).

### **General health**

Health-related quality of life is measured EQ-5D and thermometer Points are given from 0 to 100 (38).

### **General statistical considerations**

The primary data analysis will be performed based on the intention-to-treat principle.

Baseline data (parity, previous low back pain) for the two groups will be compared: For quantitative data a t-test will be applied if the data are sufficiently normal, otherwise the Kruskal-Wallis test will be applied. Qualitative data will be compared by the Fisher or chi-square test, the latter being applied if the condition of the expected values being larger than 5 is fulfilled.

A t-test will be applied to compare the mean of the primary outcome in the two groups. Similarly secondary outcomes will be compared using t-tests. For the secondary outcomes, the p-values will be adjusted for multiple testing using the Benjamini-Hochberg correction method (ref). If the data are not sufficiently normally distributed, a transformation will be applied if possible.

To explore the impact of parity and previous low back pain score on the outcomes, additional linear regression analyses of the outcomes will be performed. In case of influential observations (probably only relevant for number of days on sick leave), robust regression techniques will be applied. Per- protocol analysis will be performed of the pregnant women who perform  $\geq 75\%$  of all training sessions. The significance level will set at 0.05.

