### Strategy in case of missing outcomes

For outcomes with less than 5 percent missing data, complete case analyses will be reported. If the percentage of missing data exceeds 5, a sensitivity analysis based on worst-best and best-worst imputation will be applied (in the experimental arm imputing the worst / best outcomes observed in the control arm to the missing outcomes and vice versa for the control arm). In case these analyses give rise to the same conclusion as the complete case analyses, the latter will be reported. Otherwise data will be assumed Missing At Random (MAR) and analyses will be performed using Maximum-Likelihood or Inverse Probability Weighting.

| Primary outcome                        | Description                                                                                                                                                                                         | Handling of partly missing outcomes                                                            |
|----------------------------------------|-----------------------------------------------------------------------------------------------------------------------------------------------------------------------------------------------------|------------------------------------------------------------------------------------------------|
| Low back pain                          | Three numeric 11 point box scales (pain now, worst pain in the past two weeks, average pain in the past two weeks), 0 indicating no pain to 10 indicating worst pain imaginable.                    |                                                                                                |
| Secondary outcome                      |                                                                                                                                                                                                     |                                                                                                |
| Days spend on sick leave               | Number of days spend on leak leave,

1. Due to pregnancy-related complications.

2. Sickness or conditions with no relation to the pregnancy.

3. Due to the work environment.    |                                                                                                |

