### **Data Collection**

All information regarding participants is protected by law concerning the processing of personal data and Law about patients' legal position.

Background Data: Prior to randomization collected information about the woman's socio-demographic characteristics, height and weight, lifestyle factors (smoking, exercise, alcohol.),

Abuse and medical, gynecological and obstetric history, incl. fertility treatment, previous preterm birth and previous pelvic instability diagnosed by a physical therapist or doctor. This information is collected as part of the general systematic collection of medical records, which were held in Obstetric Clinic at Rigshospitalet.

Data on the current pregnancy and delivery: For all participants gathered information about complications in pregnancy and during labor, gestational age at birth, the children's weight and length at birth, and children's condition immediately after birth. These data are collected by chart review after birth. Information on low back pain and sick leave: Information collected in a questionnaire handed out at baseline in 16-17 weeks of pregnancy and sent to the participating women at follow up in the 32nd week of pregnancy.

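### The primary t-test ignores the baseline pain score; a baseline-adjusted model would be more precise and needs no new data

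*Protocol*

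**What the plan says.** Under Outcome variables / endpoints the Protocol states: "Primary end-point is the intensity of low back pain". The time point is set in the same place: "Outcome variables / endpoints measured in the 32nd week of pregnancy". The scale table under Strategy in case of missing outcomes describes the measure as "Three numeric 11 point box scales (pain now, worst pain in the past two weeks, average pain in the past two weeks".

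The pain questionnaire is completed twice. The questionnaire section's heading reads "Measured at baseline and at 32 weeks of gestation", and Data Collection agrees for the first occasion: "Information collected in a questionnaire handed out at baseline in 16-17 weeks of pregnancy".

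General statistical considerations names the primary test: "A t-test will be applied to compare the mean of the primary outcome in the two groups". No covariate is mentioned. Secondary outcomes are compared in the same way. Baseline pain and parity appear afterwards, in a subordinate role: "To explore the impact of parity and previous low back pain score on the outcomes, additional linear regression analyses of the outcomes will be performed".

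The sample size assessment uses a difference of 1.35 and an SD of 3.0, with no reduction for a baseline measurement.

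**The concern.** When the outcome scale is also measured at entry, part of the variation in week-32 pain can be predicted from the entry score. A t-test of the week-32 means leaves that part in the error term, so the confidence interval is wider than it needs to be. It also leaves in the estimate whatever chance difference in baseline pain the randomisation produced.

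The Protocol itself treats parity and previous low back pain as the variables that matter. They are the two examples it gives for the baseline comparison, and they are the covariates of the additional regressions. Yet they are absent from the analysis that decides the trial. The choice of primary test is stated in the Protocol, so it is not a detail left open for a later analysis plan.

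**Working it through.** **Inputs.** From the Sample size assessment: difference 1.35, SD 3.0, two-sided 5%, power 90%, 150 per group, and 70% of pregnant women with low back pain. The correlation r between baseline and week-32 pain is not in the Protocol; 0.2 to 0.6 is assumed.

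**The plan's own figure.** The normal-approximation formula is n per group = 2 × SD² × (1.960 + 1.282)² / difference² = 2 × 9 × 10.51 / 1.8225 = 103.8, so 104. With the t distribution it is 105. The stated 150 is recovered as 105 / 0.70 = 150. The Protocol does not show this step, so it is a reconstruction. It implies that the stated 90% power corresponds to 105 women per group; with all 150 per group at a difference of 1.35, power is about 97%.

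**Effect of adjustment.** Adjusting for baseline multiplies the residual variance by 1 − r², so the residual SD is 3.0 × √(1 − r²). The 95% CI half-width at 150 per group is 1.968 × residual SD × √(2/150), where 1.968 is the t quantile on 298 degrees of freedom. Power comes from the noncentral t distribution. The additional contribution of parity is not counted.

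| r (assumed) | Variance removed | Residual SD | CI half-width, 150 per group | Power, 105 per group, difference 1.35 | Power, 150 per group, difference 1.35 |
|---|---|---|---|---|---|
| 0 (t-test) | 0% | 3.00 | 0.68 | 90% | 97% |
| 0.2 | 4% | 2.94 | 0.67 | 91% | 98% |
| 0.3 | 9% | 2.86 | 0.65 | 93% | 98% |
| 0.5 | 25% | 2.60 | 0.59 | 96% | 99% |
| 0.6 | 36% | 2.40 | 0.55 | 98% | 99.8% |

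The degrees of freedom spent on two covariates do not change these figures at the precision shown.

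**Chance imbalance.** If the baseline SD is also 3.0 (assumed), a chance difference in mean baseline pain of up to about 0.68 points lies within its 95% range at 150 per group. With equal SDs, the share carried into the unadjusted week-32 difference is r times that: 0.2 × 0.68 = 0.14, 0.5 × 0.68 = 0.34 and 0.6 × 0.68 = 0.41 points, against a planned effect of 1.35. The t-test's standard error already allows for this on average, so it is a loss of precision and not a bias.

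**The case against.** The strongest reply is that nothing here is wrong. A t-test of two randomised groups is valid, and it matches the basis of the sample size. The Protocol also already plans regressions on parity and previous pain score, so the adjusted result may be available anyway and only its rank is in dispute. All of this stands. It limits the point to efficiency, but it does not explain why the less precise analysis should be the deciding one. It is also unclear whether the previous score means the baseline value of the same scale.

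The size of the gain is open to challenge too. Without r it cannot be fixed, and at r = 0.2 it is small. With 150 analysed per group and the planned difference, power is high either way.

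A reader might infer several stronger things that the Protocol does not support:

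- *Randomisation is simple and unstratified.* The Design section gives a 1:1 ratio and a computer system and is silent on strata and blocks. Silence is not a statement.
- *About 30% of women are pain-free at baseline.* The 70% figure has no time point, so it does not describe weeks 16-17.
- *The trial is underpowered without adjustment.* Diluting the effect to 0.70 × 1.35 = 0.945 gives 78% power at 150 per group, rising to 81%, 84%, 88% and 92% for r of 0.3, 0.4, 0.5 and 0.6. But 0.945 is not a Protocol figure. The planned inclusion of 550 with 25% dropout would leave about 550 × 0.75 / 2 = 206 per group, where power at 0.945 is already 89%.
- *Having both analyses invites selective emphasis.* The Protocol ranks them, and the change proposed below also keeps both, so it would not by itself remove such a risk.

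**Conclusion.** The point holds as an efficiency weakness. The primary test sets aside a baseline measurement of the outcome that the trial collects and already intends to use in a lesser analysis. The cost is a wider confidence interval and a main estimate that carries any chance baseline imbalance. There is no threat to validity or to the type I error rate.

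The benefit is small at r = 0.2 and material at r = 0.5 or above. How far it shows as power depends on how many women are analysed: several percentage points at 105 per group, little at 150 per group with the full 1.35. The direction is secure, since baseline adjustment at this sample size costs essentially nothing even if r is low. The amount is not, because it rests on an assumed r and on an SD of 3.0 at week 32.

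**What to change.** In General statistical considerations, replace the primary t-test by a linear model of the week-32 pain score on arm, adjusted for the baseline value of the same pain scale and for parity. Report the adjusted mean difference with its 95% CI. Use the matching baseline-adjusted model for the RMDQ and EQ-5D scores. Keep the t-test as a supporting analysis.

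Three details need to be written down with it:

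1. **Which scale.** The model needs one designated pain scale. The Protocol lists three and names none as primary; its sample size rests on highest pain. Use whichever is designated, at both time points.
2. **Timing.** State that the baseline pain score is taken before allocation. Data Collection says this for background data but not explicitly for pain.
3. **Missing baseline scores.** Keep these women in the model, for example by simple imputation of the baseline value without regard to arm.

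The cost is a few sentences and about one degree of freedom per covariate. No new data are needed, and the sample size need not change.

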### **Sample size assessment**

Sample size calculation was based on the following conditions:

2 points reduction on a numerical pain scale of 0-10, for the patient experiencing a reduction in pain as clinically important.

- The Average highest pain at baseline is 5.8 and SD = 3 (3; 35). –A total of 70% of all pregnant women who experience low back pain.
- We assume that the effect of the intervention is 2.0 points if all participants complete the full program.
- It is estimated that 50% of participants follow the program for at least 75% of the sessions (high participation, 19-24 sessions) while 35% follow 50-75% (moderate participation, 12 - 18 sessions) and 15% follow less than half of the program (low participation). We estimate that the effect of high participation in the training course is a reduction of 2 points, the effect of moderate participation in the training course is a reduction of 1 point, while low participation does not result in a reduction. This gives an overall reduction in the intervention group of 1.35 points ( $0.50 * 2 + 0.35 * 1 + 0.15 * 0 = 1.35$ ). A difference in pain level of 1.35 (SD = 3.0) will be available with a power of 90% and a significance level of 5% (two-sided) with 150 participants in each group.

[figure not shown]

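### The transformation rule does not exempt the primary pain outcome, so the main test could move, after the data are seen, from a difference in points to a scale the trial was not planned on

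*Protocol*

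**What the plan says.** Protocol, General statistical considerations, fixes the primary test: "A t-test will be applied to compare the mean of the primary outcome in the two groups". Secondary outcomes are to be compared in the same way, with adjusted p-values. The paragraph then ends: "If the data are not sufficiently normally distributed, a transformation will be applied if possible". This closing rule speaks of the data in general and follows the sentences on both kinds of outcome. The next paragraph, on regression, does remark that influential observations probably matter only for sick-leave days. No such remark narrows the transformation rule.

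Protocol, Sample size assessment, works in raw points throughout. The reduction called clinically important is "2 points reduction on a numerical pain scale of 0-10, for the patient experiencing a reduction in pain as clinically important". The expected effect is set out as "This gives an overall reduction in the intervention group of 1.35 points", and the planning statement reads "A difference in pain level of 1.35 (SD = 3.0) will be available".

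**The concern.** The trial is planned on a difference in mean pain in points. If the data are judged not normal enough, the written rule moves the primary test to another scale. Its null hypothesis is then equality of mean log pain or mean root pain, and the result cannot be read directly against 1.35 or 2 points. The scale would also be settled after the outcome data are seen, for the one test that most needs to be fixed beforehand.

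The trigger is plausible. The outcome is an 11-point box score, the inclusion criteria do not require pain, and the sample size section lists "A total of 70% of all pregnant women who experience low back pain". Many zeros at week 32 are therefore likely, although the protocol does not give that distribution.

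**Working it through.** **1. The planning figure, in points.** Inputs from Sample size assessment: effects of 2, 1 and 0 points in 50%, 35% and 15% of women; SD 3.0; two-sided 5%; power 90%.

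- Effect: 0.50 × 2 + 0.35 × 1 + 0.15 × 0 = 1.35 points.
- n per group = 2 × (1.960 + 1.282)² × 3² / 1.35² = 103.8, so 104.
- The stated 150 is recovered, within rounding, as 104 / 0.70 = 149. The text does not spell out that step. Taken literally, 150 per group gives 97.4% power for 1.35 points.

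Every input is on the raw 0-10 scale.

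**2. What a transformation does to two points.**

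| Fall in pain | Points | log(x+1) | square root |
|---|---|---|---|
| 8 to 6 | 2 | ln 9 − ln 7 = 0.25 | 2.83 − 2.45 = 0.38 |
| 2 to 0 | 2 | ln 3 − ln 1 = 1.10 | 1.41 − 0 = 1.41 |

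The same two points count about 4.4 times as much at the bottom of the scale on the log (1.10 / 0.25) and about 3.7 times as much on the root (1.41 / 0.38).

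**3. Equal means in points, different shapes.** This is a constructed example with 150 per group and 20,000 simulated trials. One group has 30% zeros and otherwise a rounded normal (mean 5.0, SD 2.2) clipped to 1-10. The other is a rounded normal with SD 1.5 clipped to 0-10. Raw means are 3.51 and 3.52. Rejection rates are raw 5.1%, square root 84%, log(x+1) 86%. The transformed test answers a different question.

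**4. Would the trigger fire?** A Shapiro-Wilk test on 300 women rejected normality in all 300 simulated data sets with 30% zeros. It also did so in all 300 drawn from a rounded, clipped normal with the protocol's mean 5.8 and SD 3. The protocol names no criterion, so a more lenient judgement could differ.

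**5. Is the rule needed?** With 30% zeros, and otherwise a rounded normal (mean 5.8, SD 2.2) clipped to 1-10, 150 per group and no effect, the raw t-test rejected in 5.1% of 20,000 trials. Non-normality of this kind does not call for a transformation at this size.

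**6. Power, if a scale were simply imposed.** 150 per group; the shapes are assumptions.

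| Scenario | Raw | Square root | log(x+1) |
|---|---|---|---|
| 30% zeros in both groups, difference 1.29 points | 97% | 71% | 71% |
| 30% zeros in both, planned adherence mix only in women with pain, difference 0.90 | 74% | 40% | 40% |
| As above, wider spread | 61% | 42% | 41% |
| Near-normal, mean 5.8, SD about 3 (two variants) | 97%; 91% | 96%; 90% | 95%; 90% |
| Right-skewed | 90% | 84% | 84% |
| Exercise prevents pain (zeros 30% against 53%) | 95% | 98% | 98% |

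**7. Would log or root be chosen on normality?** In a model with 30% zeros and the planned adherence mix, power was 76% raw, 46% log and 48% square root. However, raw was the most normal scale in 1,996 of 2,000 trials, so choosing by normality left power at 76%. In right-skewed models with a lower mean, where square root or log usually was chosen, power stayed within about 1 point of raw.

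**The case against.** The strongest reply rests on the words *if possible*. The rule exists to improve normality, and no transformation removes a spike at zero. If many women score zero, an analyst following the rule's purpose would find that log and root make matters worse and would stay with raw points. Step 7 bears this out, and this part of the objection stands.

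It disposes of a stronger reading that a reader might infer: that the rule would cost the primary test about 30 points of power. That figure needs about 30% zeros in both groups, an effect confined to women with pain, and an analyst who applies log or root although it worsens normality. The documents supply none of these as facts. The 70% is not stated to be the share scoring above zero at week 32, and it may serve only to inflate the sample size. The SD of 2.2 among women with pain is also an assumption; the protocol gives SD 3.

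Two further replies carry less weight. The function, the normality criterion and any back-transformation may properly be left to a statistical analysis plan, and their absence is not the complaint. The protocol itself, though, states that the scale of the primary test depends on the data, and a plan that follows it inherits that rule. A transformation fallback is also conventional, and a raw difference could be reported beside it. The p-value and the estimate would then answer different questions.

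**Conclusion.** The point holds as one of estimand, interpretability and pre-specification. As written, the rule allows the primary test to leave the scale on which the trial is sized and clinical importance is defined, on a trigger judged after the data are seen. It gains nothing needed in return, since the raw t-test keeps its error rate near 5% at about 150 per group even with an assumed 30% zeros.

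No general loss of power is shown. Outside the scenarios with heavy zeros in both groups, imposing log or square root changes power by between about +3 and −6 points. When the scale is chosen for normality, the simulated change is about 1 point or less. All of these figures depend on assumed week-32 distributions. The conclusion about the estimand does not. It concerns the primary pain outcome only and says nothing against transforming sick-leave days.

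**What to change.** Exempt the primary outcome from the transformation rule and state, for low back pain:

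> The primary outcome is analysed as the difference in mean pain, in points on the untransformed 0-10 scale, with a 95% confidence interval and unequal-variance (Welch or robust) standard errors, whatever its distribution. A permutation test or bootstrap interval for the same mean difference is the sensitivity analysis.

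The rule can remain for secondary outcomes. The change is a short addition to the analysis section and needs no further data or participants, so it is a free improvement. All that is given up is the option of a transformed primary test that might, in some settings such as prevention of pain, have slightly more power.
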